## Background

Tuberculosis (TB) is an airborne infectious disease that affects almost nine million people each year, mainly in resource-limited settings [1]. The predominant global strategy for identifying people with TB is 'passive case detection’, which relies upon a diagnosis of TB being made in symptomatic patients presenting to healthcare facilities for evaluation [2]. This approach is predicated upon the assumption that most patients will be symptomatic. However, despite the widespread adoption of this approach in high-prevalence countries, only 65% (63 to 68%) of the estimated total number of patients with TB are diagnosed each year [3]. Those patients who are not diagnosed are not treated, and are therefore at risk of transmitting the infection to others. If the Stop TB Partnership’s goal of global TB elimination by 2050 is to be realized [4,5], new evidence-based strategies for enhancing case detection are urgently needed.

### Rationale for the study

Recent prevalence surveys in countries with a persistently high prevalence of TB have found that a substantial proportion of disease is not detected by conventional passive case-finding strategies [6-8]. Strategies that increase the proportion of cases that are detected may interrupt ongoing transmission of *M. tuberculosis*, and reduce the prevalence of TB over time [9,10]. Case detection strategies that target high-risk populations and are integrated with national TB control programs [11] are most likely to be feasible and sustainable.

Contacts of patients with TB are known to have a high risk of developing the disease, particularly in the five years after exposure. A recent meta-analysis of studies including almost 900,000 contacts showed that 3.1% (95% confidence interval (CI), 2.2 to 4.4%) of contacts in studies from resource-limited settings and 1.4% (95% CI, 1.1 to 1.8%) of contacts in studies from high-income countries had co-prevalent TB [12]. In Vietnam, our previously reported cohort study of active case finding in tuberculosis (ACT1) found that among 545 household contacts, 0.7% had co-prevalent disease [13]. Consequently, contacts are a potentially high-yield population to screen for disease. Close contacts of TB patients are also identified relatively easily by TB control programs, which can build upon their existing therapeutic relationship with the TB patient. For these reasons, contact investigation, defined as the evaluation of contacts of known TB patients for disease or infection is potentially a worthwhile adjunct to an effective TB control program in resource-limited settings.

Although contact investigation has been standard practice in most high-income countries for many years [14-17], it has been much less commonplace in resource-limited settings. Contact investigation policies in these settings have generally focused on specific high-risk contacts, such as children [18,19] and people living with HIV [20]. Recent World Health Organization (WHO) guidelines for TB contact investigation recommended the intervention be extended to close contacts in settings where adequate resources are available [21]. However, the expert panel acknowledged that the quality of the available evidence for the practice was very poor, according to GRADE criteria [21]. Although many published studies report a high yield among contacts, few assess the effectiveness compared with standard passive case finding [22]. There have been few randomized controlled trials of household contact investigation published to date [23,24].

Strategies for enhanced case detection in high-prevalence settings must be feasible and cost-effective, so that they are appropriate and affordable in the local context. It is important that countries considering implementing contact investigation have a high rate of DOTS coverage and consistently high treatment completion rates, so that additional cases identified by enhanced case detection are likely to be treated successfully [25,26]. In order to be informative to health policy makers, this study is designed so that the intervention that is being evaluated can be implemented and scaled up within the busy and resource-limited environment of the Vietnamese healthcare system.

### The research context

Vietnam is a middle-income country that is ranked eleventh in TB burden among the high-prevalence countries. A national survey in 2006 estimated that the prevalence of TB was 307 bacteriologically proven cases per 100,000 adults (95% CI, 249 to 366 per 100,000 persons aged 15 and over) [7]. Despite consistently achieving WHO targets for treatment completion rates since 1998, annual case notifications have not yet declined. Based on data from the prevalence survey and routine reporting, the WHO estimates that only 56% (95% CI, 44 to 73%) of all cases are diagnosed [1]. These data suggest that the Vietnamese National Tuberculosis Program (NTP), which oversees the majority of TB control in the country, may need to consider new approaches to identify disease in the population.

The Active Case Finding of Tuberculosis (ACT2) study is a cluster randomized controlled trial of contact investigation that is conducted by staff of the NTP, based at local district health facilities, and integrated within the management structure of the NTP.

### Hypothesis and aims

The hypothesis of this study is that, in countries that are highly endemic for TB, targeted active case finding among household contacts will result in more contacts being diagnosed with TB than will standard passive case finding alone.

The primary aim of the study is to determine if household contact investigation is effective, by determining whether it increases the overall yield of active TB diagnosed among household contacts of patients with smear-positive TB compared with usual passive case detection. There are two secondary aims. The first is to estimate the cost effectiveness of this intervention by measuring the incremental cost-effectiveness ratio. The second is to determine the feasibility of implementing contact investigation within the NTP in a range of settings in Vietnam, including urban and rural environments. The screening strategy proposed in this study will be operationally nested within the NTP.

## Methods/Design

This is a cluster randomized controlled trial with two arms comparing standard passive case detection with household contact investigation in eight provinces in Vietnam. In the active intervention clusters, household contacts of patients with TB will be assessed for the disease four times over a two-year period. The assessment comprises clinical evaluation, chest radiography and, in TB suspects, microbiological testing of sputum.

### Inclusion and exclusion criteria

All patients aged 15 years or over with pulmonary TB and at least one sputum sample positive for acid-fast bacilli on direct smear microscopy will be eligible to enter the study. Patients are excluded if they have no eligible household contacts.

Household contacts of any age are eligible for inclusion if they lived in the same dwelling as the index patient during the two months prior to the diagnosis of the index patient. Pregnant women are eligible for inclusion, but women known to be pregnant are not offered a chest radiograph.

### Study endpoints

The following endpoints are being measured in all contacts (in both groups). The primary endpoint is the proportion of contacts with clinically diagnosed TB. This will be ascertained based on the results of screening (in the active screening districts) and routine notifications to the NTP (in the active screening and control districts). Secondary endpoints, as indirect measures of study feasibility, are: (a) the weighted proportion of contacts with microbiologically proven TB (defined as either smear or culture positive TB), smear-positive TB and extrapulmonary TB; (b) cost effectiveness, determined by calculating the direct and indirect costs for each additional case diagnosed; and (c) the proportion of eligible contacts enrolling in the study, and the proportion of contacts participating in scheduled follow-up.

### Description of intervention

#### *Recruitment of index cases*

Index cases with smear-positive pulmonary TB and their contacts are identified in both active and control study districts. The study intervention is only implemented for contacts in the active intervention districts.

Consecutive patients with smear-positive pulmonary TB, who live in the study districts, are identified by TB staff working within district hospitals or district tuberculosis units. Those who agree to participate are given a participant information statement and asked to sign a written consent form.

#### *Recruitment of contacts*

Contacts are identified using a screening questionnaire completed in consultation with the index case. Household contacts include all members of the household occupied by the index case, including children and infants, who were present during the period of recent infectivity, that is, two months up to the time of diagnosis. Household contacts are approached by the index patient in their family and given information explaining the study. Contacts are invited by the patient to enroll in the study at a district clinic.

#### *Active intervention*

All contacts in the active intervention districts will be evaluated at the time they are first identified, and then 6, 12, and 24 months post-exposure. The procedures will be free of charge to the participants. On each occasion, the assessment will include a symptom questionnaire, physical examination, and chest X-ray. Contacts will have a chest X-ray at a local clinic or nearby private radiology service. X-ray films will be read by local clinical staff for routine clinical action and then be transferred to a central location for standardized re-reading by provincial level staff.

Contacts will be defined as having possible TB if they have: (a) cough lasting for two weeks, (b) sputum for two weeks, (c) any hemoptysis, or (d) an abnormal chest X-ray meeting the criteria for possible TB. Contacts meeting one or more of these criteria will be asked to submit two spontaneous sputum specimens collected on consecutive days for acid-fast bacilli (AFB) examination. Two direct smear examinations and one culture test will be undertaken in the Provincial Hospital laboratory. For children younger than five years, the diagnosis of TB will be made on clinical and radiological grounds, in accordance with local policy at the time of commencement of the study. Treatment of active disease will be according to the policies of the NTP. An experienced clinician in each province will be available to advise district staff regarding the diagnosis of childhood TB and the investigation of suspected extrapulmonary disease.

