**Methods/Design:**

We will conduct a cluster randomized controlled trial of contact investigation within the national tuberculosis control program of Vietnam. Household contacts of patients with smear-positive pulmonary tuberculosis will be invited to attend district tuberculosis units for symptom screening, examination, and chest radiography on four occasions over a two-year period. The primary endpoint is clinically confirmed tuberculosis among contacts during the 24 months of follow-up, ascertained using capture-recapture analysis. Microbiologically proven tuberculosis and treatment completion rates among contacts diagnosed with tuberculosis will be secondary endpoints. The incremental cost-effectiveness ratio will be estimated. The study will have 80% power to detect a 50% increase in the primary endpoint in the active intervention arm compared with the control arm. The study will include 8,829 contacts in each of the active screening and control groups, within 70 districts in 8 provinces in Vietnam, in both rural and urban settings.

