### Control districts

Contacts enrolled in control districts, will be given general information about the typical symptoms of TB and advised to report to the district hospital or TB unit if they develop these symptoms. During the study period, self-referring contacts with TB, who are participating in the study, will have two sputum specimens transferred to the reference laboratory for culture, in addition to any routine diagnostic procedures. This will allow comparison of rates of culture-confirmed TB between active and control districts. Contacts diagnosed with TB in both the control and active intervention groups will receive standard treatment for TB through the NTP.

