### Primary and secondary endpoints and stratification

The primary endpoint will be the weighted proportion of contacts with clinically diagnosed TB in screening and control districts during the two-year follow-up period of the study. Secondary endpoints will include the weighted proportion of contacts with microbiologically proven TB, smear-positive TB, and extrapulmonary TB. We will also estimate the proportion of contacts with TB who complete treatment. Stratum specific weighted prevalence rates of clinically diagnosed and microbiologically proven TB will be determined for region and rurality.

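### The last screen of the active arm falls where the 24-month count closes, so some earlier diagnoses will be counted as additional ones

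*Protocol article*

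**What the plan says.** The Active intervention section states that contacts in active districts "will be evaluated at the time they are first identified, and then 6, 12, and 24 months post-exposure". The abstract places all four assessments inside the counting period: "symptom screening, examination, and chest radiography on four occasions over a two-year period". The primary endpoint is the weighted proportion with "clinically diagnosed TB in screening and control districts during the two-year follow-up period of the study".

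In control districts, contacts are informed about symptoms and "advised to report to the district hospital or TB unit if they develop these symptoms". Under Study endpoints, cases come from screening plus routine notifications in active districts, but from routine notifications alone in control districts.

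The hypothesis is that active case finding "will result in more contacts being diagnosed with TB than will standard passive case finding alone". The effect measure is a relative risk (Analysis of effectiveness). The cost-effectiveness ratio divides the cost difference by the difference in cases detected (Analysis of cost effectiveness).

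**The concern.** The screens at entry, 6 and 12 months each leave controls at least a year in which the same disease can surface through self-referral. The month-24 screen leaves none. Of the disease it finds, one part would never have been diagnosed passively, which is the gain the trial is looking for. The other part would have been notified a few months later. In the control arm that second part falls outside the window, so it enters the comparison as an extra case although only its date has changed.

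Both the primary relative risk and the denominator of the cost-effectiveness ratio take it in. At stake is how far the result supports the stated claim that more contacts are diagnosed, and what each additional case costs.

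**Working it through.** **The plan's own figure.** For 2.3% versus 3.45% (a 50% increase), two-sided 5% (inferred, since alpha is not stated), 80% power and pooled variance:

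n = [1.96 x sqrt(2 x 0.02875 x 0.97125) + 0.842 x sqrt(0.023 x 0.977 + 0.0345 x 0.9655)]^2 / 0.0115^2 = 3,313 per group, as stated. The design effect is 1.3 x 2.05 = 2.665, and 3,313 x 2.665 = 8,829, as stated.

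The narrative in the same section (2.3% prevalence, about half without typical symptoms, screening finding 75%) could also be read as 1.15% versus 1.725%. That contrast needs about 6,726 per group, so it is not the one behind the stated number.

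**Rough guide to the yield of one exit screen.** Inputs are a prevalence of "307 bacteriologically proven cases per 100,000 adults" (The research context) and a screening yield of 75% (Sample size calculation).

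- 0.307% x 0.75 = 0.23 points.
- On 2.3% versus 3.45%: 0.23/1.15 = 20% of the planned difference; 0.23/2.3 = 0.10 on the relative risk.
- On 1.15% versus 1.725%: 0.23/0.575 = 40%; 0.23/1.15 = 0.20.
- Keeping only the 56% of cases estimated to be diagnosed nationally: 0.23 x 0.56 = 0.13 points, or 0.13/2.3 = 0.06 on the relative risk. If earlier screens have halved the pool (an assumption), this becomes about 0.03.

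Contacts carry a higher risk than the general adult population, which works in the other direction.

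**Effect on cost.** With the cost difference held fixed, if a share f of the detected difference is only brought forward, the cost per truly additional case is 1/(1 - f) times the reported one: 1.25 times for f = 20%, 1.67 times for f = 40%.

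**Illustrative model.** Assumptions that are not in the document: undiagnosed prevalence at entry 0.7 to 1.15%, onset 0.3 to 0.6% per year, exponential delay to passive diagnosis. Sensitivity per screen is 75%. First suppose that every case would eventually be notified, so that the true extra yield is nil:

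| Mean passive delay | 24-month RR | RR without exit-screen cases | RR with notifications followed to month 36 |
|---|---|---|---|
| 3 months | 1.03-1.07 | 1.00 | 1.00 |
| 6 months | 1.09-1.15 | 1.02-1.03 | 1.01-1.02 |
| 12 months | 1.27-1.40 | 1.16 | 1.08-1.10 |

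Now suppose that only 56% would ever be found passively. The 24-month RR is 1.81-2.45. Removing only the brought-forward exit-screen cases gives 1.78-2.21. Removing all exit-screen cases gives 1.54-1.97, lower because true extra yield is dropped as well.

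**The case against.** The strongest reply is that diagnosis within two years, with the same window in both arms, is a legitimate estimand. Earlier detection is also part of the rationale: the Background hopes to interrupt transmission, and the Discussion expects serial radiographs to month 24 to find and treat disease. This stands as a reason to keep the 24-month primary analysis. It does not remove the need to separate earlier from additional diagnosis, because the hypothesis and primary aim are worded as more cases and higher overall yield.

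A reader might infer that all disease found at the exit screen is artefact, or that the relative risk is inflated by 0.20. The document does not support this. With 56% of cases diagnosed nationally and about half of prevalent cases lacking typical symptoms, many exit-screen cases would never have been notified. The 0.20 figure also rests on a control proportion that does not reproduce the stated sample size.

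A reader might also infer that the trial could declare a benefit where none exists. The worrying range of 1.27-1.40 needs both a 12-month mean delay and eventual passive diagnosis of every case, and the second sits badly with the 56%. With 56%, the modelled relative risk stays far above 1 either way.

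The abstract says "The primary endpoint is clinically confirmed tuberculosis among contacts during the 24 months of follow-up, ascertained using capture-recapture analysis". Capture-recapture addresses cases missed by the sources. Nothing in the article presents it as a correction for timing, and only one source is named for control districts.

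Finally, sensitivity analyses are often left to an analysis plan that is not shown here. Their absence is therefore not the point. The point is the timing, which the article fixes.

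**Conclusion.** The concern holds as a statement about the design. The exit screen coincides with the end of counting, only one arm has it, and cases notifiable soon afterwards are credited to that arm alone. The direction is known: the relative risk is too high and the cost per additional case too low, as measures of additional diagnosis.

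The size is not known, because passive delay and incidence in contacts are not given. A guide of 0.10 on the relative risk (0.20 on the other reading of the sample-size text), before allowing for depletion and never-diagnosed cases, is the most that the document's figures support. With those allowances it may be a few hundredths, and higher risk in contacts could raise it again. The effect bears on the effect size and the cost-effectiveness ratio more than on the sign of the result. It does not invalidate the 24-month comparison.

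**What to change.** Keep the visits and the 24-month primary analysis as they are.

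1. Pre-specify the 24-month relative risk and cost-effectiveness ratio also without cases first found at the month-24 screen, and state whether that screen's costs stay in the numerator. Label this a sensitivity analysis that removes most of the exit-screen lead time. It is not a strict lower bound: it drops true extra yield, and some lead time from the month-12 screen remains (1.16 in the 12-month row of the table, where the true value is 1).
2. Where notification data allow, follow notifications equally in both arms for a fixed catch-up period, for example 6 to 12 months, as a supportive analysis.
3. Word any claim of additional cases in the light of both results.

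The first step needs no new data. The second needs a later register extract and delays that supportive estimate only. Its relative risk will be somewhat diluted by cases with onset after month 24, which is one reason not to make it primary. No visit or test is added.

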### Control districts

Contacts enrolled in control districts, will be given general information about the typical symptoms of TB and advised to report to the district hospital or TB unit if they develop these symptoms. During the study period, self-referring contacts with TB, who are participating in the study, will have two sputum specimens transferred to the reference laboratory for culture, in addition to any routine diagnostic procedures. This will allow comparison of rates of culture-confirmed TB between active and control districts. Contacts diagnosed with TB in both the control and active intervention groups will receive standard treatment for TB through the NTP.

### Selection of study districts

The study will be conducted in 70 districts within eight provinces. These provinces have been selected to include four provinces in the south (Ho Chi Minh City, Can Tho City, and the rural provinces of An Giang and Tien Giang), where the prevalence of TB is highest, two provinces from the central area (Da Nang Province and the rural province of Binh Dinh), and two provinces from the north (Hanoi City and the semi-rural province of Vinh Phuc). This geographic and urban-rural stratification is important because the incidence of TB increases from the north to the south within Vietnam [7]. There are also substantial differences in lifestyle and infrastructure between rural and urban areas. Hence, the selection of this diverse range of sites will increase the generalizability of the study findings.

### Randomization

Among the 97 districts within these eight provinces, 70 have been randomly selected for participation in the trial. These districts were selected with a probability proportional to their population size. The initially selected districts will enter a run-in period, prior to randomization, during which time they will be required to recruit two patients and six contacts and to demonstrate that they have the necessary resources to conduct the study. If districts fail or withdraw during this pre-randomization run-in period, they will be replaced by the next randomly selected district.

We will randomly allocate districts to the active intervention or control group using the minimization method with predefined randomization lists [27]. The minimization criterion will be province, to ensure balance of intervention and control districts within each province. District size will not be taken into account in the randomization process. Randomization will be performed by a person who is not otherwise engaged in the project, and is blinded to the identity of districts.

